### Missing data

Primary statistical analyses will be run on an intention-to-treat basis, whereby all participants are included according to their group allocation and irrespective of their adherence to the intervention. Secondary analyses will be performed to account for non-adherence to the intervention. Per-protocol analyses will be run, excluding participants from the intervention group who spent hardly any time on the Hub (e.g. visited the Hub only once). In additional analyses, adherence scores will be entered either as a categorical or continuous factor in the statistical analyses (e.g. repeated measures analysis of variance) to identify whether non-adherence or low-adherence alters the outcomes in the intervention group. At follow-up, we expect quite a bit of dropout and thus missingness of data with respect to the primary and secondary outcomes. Based on inspection of the data (i.e. amount of missingness and validity of underlying assumptions), the most appropriate approach for handling missing data (e.g. complete case analysis, single imputation, model-based methods, multiple imputation) will be chosen as no additional outcome data will be collected from participants who have withdrawn.

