### Study design

A cRCT will be conducted with SMEs in two conditions, intervention and control, within each of the three sectors: healthcare, construction and ICT. Quantitative and qualitative evaluation data will be obtained and guided by the RE-AIM framework [57] and the evaluation framework of Proctor et al. [58], to structure the outcome, process and economic evaluation of the MENTUPP intervention from data collected at baseline, 6-month and 9-month follow-ups. Five types of evaluation measures will be collected: six validated questionnaires, two self-developed surveys, a monitoring instrument and user data from the MENTUPP Hub. Focus groups conducted with the local research officers post-intervention will inform process evaluation and how the Hub was implemented locally. The intervention group will complete the baseline survey and receive immediate access to the MENTUPP Hub. They will also complete the 6-month and 9-month follow-up measures. The control group will complete the baseline, 6-month and 9-month measures. Following the completion of the 9-month measures, participants of the control group will receive access to the MENTUPP Hub (see Fig. 1 for timeline).

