### Process evaluation

Descriptive statistics will be used to analyse numeric data of the process evaluation collected via the monitoring instrument, the bespoke surveys and the user data. Qualitative data coming from the focus groups and the monitoring instrument (open text fields) will be analysed thematically. Data gathered via the focus groups with research officers will be audio recorded, transcribed, translated to English where necessary and analysed via thematic analysis. The process evaluation will be informed by the framework based on the three themes of implementation, mechanisms and context [79].

Adherence data are collected in the intervention group in three ways: via the pre-intervention survey, the post-intervention survey and the log data of the Hub. The pre-intervention survey asks participants to indicate whether they have positive expectations about the intervention at start and are intending to make use of the intervention. In the post-intervention survey, respondents are asked to indicate how much time they spent in the past months on MENTUPP-related activities. Finally, the log data of the Hub allows tracking which respondents registered for the Hub, how many times they visited the Hub, how much time they spent on the Hub and how their Hub visits are spread in time during the implementation period. Exploratory analyses will be conducted on the adherence data and results on the intention of respondents to adhere to the intervention at start, the amount of adherence during the intervention period and subsequent withdrawal from the intervention will be reported in accordance with the 2010 Consolidated Standards of Reporting Trials (CONSORT) statement.

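### The secondary per-protocol analysis drops low Hub users from the intervention arm only, so it and the within-arm adherence analysis are confounded by self-selected use; the intention-to-treat primary is unaffected

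*Protocol article*

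**What the plan says.** All the analysis statements below are in the Missing data section of the protocol article unless another section is named.

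- The primary analysis is by allocation: "Primary statistical analyses will be run on an intention-to-treat basis, whereby all participants are included according to their group allocation", whatever the adherence.
- Adherence comes second: "Secondary analyses will be performed to account for non-adherence to the intervention".
- The per-protocol rule is "Per-protocol analyses will be run, excluding participants from the intervention group who spent hardly any time on the Hub". The cut-off is given by example: "e.g. visited the Hub only once". No rule is given for controls.
- In further analyses, "adherence scores will be entered either as a categorical or continuous factor in the statistical analyses (e.g. repeated measures analysis of variance"). The stated aim is "to identify whether non-adherence or low-adherence alters the outcomes in the intervention group".
- Data analysis, Process evaluation: "Adherence data are collected in the intervention group in three ways". The same section describes the analyses of these data as exploratory.
- Study design: "Following the completion of the 9-month measures, participants of the control group will receive access to the MENTUPP Hub".
- Data analysis, Outcome evaluation names linear and logistic mixed effects models for the six survey measures.

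**The concern.** A per-protocol comparison is only as good as its two groups are alike. Here one arm is filtered on behaviour after randomisation and the other is not. The control arm still contains people who would not have used the Hub had they been offered it; their counterparts in the intervention arm have been removed.

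Use is unlikely to be a random event. The Implementation section describes voluntary, self-paced access, an advised allowance of about 20 minutes a week in work time, and a Champion who promotes engagement in each SME. Personal motivation and a supportive workplace could each drive both use and change in wellbeing. The adherence-score analysis compares heavier with lighter users inside one arm, so it has the same problem without even a randomised comparator.

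The risk is that either result is read as the effect of the Hub in those who used it. Such a figure mixes any true effect with the difference between people who choose to use the Hub and people who do not.

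**Working it through.** **1. The plan's own figure.** Inputs from Sample size: 27 SMEs × 23 = 621 per arm, difference 0.25 SD, ICC 0.05, two-sided 5%.

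- Design effect: 1 + (23 − 1) × 0.05 = 2.10.
- Effective n per arm: 621 / 2.10 = 295.7.
- Standardised difference: 0.25 / √(2 × 2.10 / 621) = 3.04.
- Power: 86.0% (normal), or 84.7% (t with 52 df, counting clusters).

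The stated 85% reproduces, so 0.25 SD is a fair yardstick.

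**2. Can controls be filtered in the same way?** No. Adherence is recorded in the intervention group only, and controls have no access until their last measures are complete. The asymmetry is built into the rule. Fixing the cut-off in an analysis plan would not remove it.

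**3. Size of the distortion when the Hub has no effect.** Neither of two inputs is in the article, so both are assumptions: f, the share of the intervention arm excluded (10% to 50%), and ρ, the correlation of Hub use with outcome change, higher meaning better (0.1 to 0.3). With both variables standard normal and the lowest f of users removed, the mean of those kept is

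bias = ρ × φ(q) / (1 − f), with q the f-quantile of the standard normal.

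| Excluded f | φ(q)/(1 − f) | ρ = 0.1 | ρ = 0.2 | ρ = 0.3 |
|---|---|---|---|---|
| 10% | 0.195 | 0.02 | 0.04 | 0.06 |
| 30% | 0.497 | 0.05 | 0.10 | 0.15 |
| 40% | 0.644 | 0.06 | 0.13 | 0.19 |
| 50% | 0.798 | 0.08 | 0.16 | 0.24 |

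The entries are in SD. As shares of the target they run from 0.0195 / 0.25 = 8% to 0.239 / 0.25 = 96%. At ρ = 0 the bias is zero. A negative ρ gives the same sizes with the opposite sign.

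**4. Check by simulation.** Trials with no effect were simulated at the planned size and ICC (1,500 per setting) and analysed by a t-test on SME means, so clustering was respected. The false-positive rate was about 20% at ρ = 0.2 with 30% excluded, and 69% at ρ = 0.3 with 50% excluded. It stayed near 5% at ρ = 0. A correct cluster-level test does not protect against the selection.

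**5. Clustering in the adherence analysis.** This is a separate matter. Leaving out the SME effect distorts the standard error and does not by itself bias the estimate. For a within-arm comparison of higher and lower users with no true association (3,000 simulations per setting), a test that ignores SME had these type I error rates, by the assumed ICC of Hub use itself:

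| ICC of use | Type I error |
|---|---|
| 0 | 5.5% |
| 0.3 | 7.5% |
| 0.5 | 9% |
| 1 (use fixed by SME) | 17% |

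**The case against.** The strongest reply is that nothing here touches the main result. Intention-to-treat is primary, the per-protocol and adherence analyses are labelled secondary or additional, and work on the adherence data is called exploratory. That stands, and it limits the weight of the point.

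The size also rests on inputs that the article does not supply. This stands too. The only exclusion example is a single visit, with no share attached. At 10% excluded the distortion is at most 0.06 SD over the assumed correlations, and it could be zero or negative.

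A reader might go further and infer four things that the article does not support:

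- **That the adherence analysis will ignore clustering.** Repeated-measures ANOVA is named only as an example, clustering is not mentioned there rather than rejected, and mixed models are named for the outcome analyses.
- **That everyone with a missing wave will be dropped.** The same section leaves the missing-data method open, including model-based methods and multiple imputation.
- **That standard errors will be too small by √2.10 = 1.45.** That factor applies only if use is constant within an SME, whereas access is individual and self-paced.
- **That the cut-off will be chosen after the logs are seen.** It is not fixed in the article, and an analysis plan may fix it beforehand.

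Finally, the instrumental-variable alternative has its own weakness. The intervention also works through leaders, Champions and the organisation, so allocation may affect people who never open the Hub. This is a fair reason to attach a caveat and to keep the planned comparisons as description. It does not make the one-arm exclusion a valid estimate of effect.

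**Conclusion.** The point holds for the secondary analyses only. The per-protocol rule compares self-selected intervention users with all controls, and the within-arm adherence analysis compares self-selected users with non-users. Each is biased as an estimate of the Hub's effect whenever use is related to prognosis. A later analysis plan could set the threshold and add covariates, but it could not restore the randomised comparison without replacing the method.

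Under the assumed 10–50% excluded and correlation 0.1–0.3, a Hub with no effect would show about 0.02–0.24 SD in its favour, up to nearly the whole 0.25 SD target. This is a range over assumptions and not an expected value: the bias vanishes at zero correlation and reverses if more distressed employees use the Hub more. The source of bias is self-selection; clustering bears only on the standard errors of the adherence analysis, by an amount that depends on how strongly use clusters by SME.

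**What to change.** 1. Make the main adherence analysis a complier-average causal effect, with randomised arm as instrument and logged Hub use as exposure at a threshold fixed before unblinding. Include baseline covariates and SME-clustered standard errors. The one-sided access and the logs already planned make this feasible.
2. State the exclusion restriction as an assumption. Leader, Champion and organisation-level effects on non-users may violate it, as may any benefit from use below the threshold. Note also that the method does not correct for differential loss to follow-up, with 65% attrition expected.
3. Keep the one-arm per-protocol and within-arm adherence comparisons only as descriptive associations, and say that they are not effects in users.
4. Fit those descriptive comparisons in the mixed models named under Outcome evaluation, with an SME random effect, and drop the repeated-measures ANOVA example.

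The cost is wording and code, with no new data. The price is precision. With one-sided non-compliance the complier effect is roughly the intention-to-treat effect divided by the share above the threshold, so its interval widens by about 1 / (1 − f): 1 / 0.9 = 1.11 at 10% below the threshold, 1 / 0.7 = 1.43 at 30%, and 1 / 0.5 = 2 at 50%.

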### Sample size

In each of the nine countries, local research officers will use convenience sampling to recruit a minimum of two SMEs in each of the three sectors, yielding a total of at least 54 participating SMEs, half for intervention and half for control. An average of 65 participants per SME will be recruited at baseline. Allowing for an estimated attrition rate of 65%, based on the pilot study and previous literature [60, 61], this will yield baseline and follow-up data for 23 participants per SME. A sample size of 621 participants (i.e. 27 SMEs with 23 participants) in each arm of the cRCT achieves 85% power to detect a difference of 0.25 standard deviations between the mean change in intervention participants and the mean change in control participants, when the intra-cluster correlation is 0.05, using a two-sided independent *t*-test with a significance level of 0.05.

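### With 65% attrition expected, the primary analysis has no default missing-data method: the choice follows inspection of the data, and single imputation and complete case are among the options

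*Protocol article*

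**What the plan says.** The Sample size section of the protocol article forecasts heavy loss. It states "An average of 65 participants per SME will be recruited at baseline", then "Allowing for an estimated attrition rate of 65%, based on the pilot study and previous literature", and concludes that "this will yield baseline and follow-up data for 23 participants per SME". The power statement rests on those who remain, 27 × 23 = 621 per arm, and says that this number "achieves 85% power to detect a difference of 0.25 standard deviations between the mean change in intervention participants".

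The Missing data section puts the primary analysis on an intention-to-treat basis in which "all participants are included according to their group allocation and irrespective of their adherence to the intervention". It expects missing primary and secondary outcomes at follow-up. On handling them it says "Based on inspection of the data (i.e. amount of missingness and validity of underlying assumptions), the most appropriate approach for handling missing data" is to be selected, with the options given as "e.g. complete case analysis, single imputation, model-based methods, multiple imputation) will be chosen". It names no default and no sensitivity analysis to missing data, and the two criteria are not turned into a decision rule.

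Two other places bear on this. The Outcome evaluation part of Data analysis specifies linear and logistic mixed effects models using baseline and both follow-ups. The section on randomisation of SMEs says that outcome analysts will be blinded.

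**The concern.** When about two thirds of follow-up values are expected to be missing, the handling method is a large part of the primary analysis. The protocol does more than leave this to a later document: it says the choice comes after the data have been looked at. A statistical analysis plan that fixed the method beforehand would depart from that sentence.

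Three features make this a weak rule.

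- **The criteria cannot do the work asked of them.** The amount of missingness is already forecast, so it is little reason to wait. The validity of the assumptions cannot be established by inspection: observed data can count against missing completely at random (MCAR), but cannot separate MAR from MNAR.
- **The options are not equally defensible.** Single imputation treats imputed values as observed, so it can misstate uncertainty or attenuate the effect. Complete case analysis sits uneasily with a primary analysis said to include all participants.
- **The section is not tied to the analysis model.** The mixed models can use every available observation by likelihood, yet model-based methods appear only as one option among four.

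At stake is whether the main result depends on a choice that could be fixed now at almost no cost.

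**Working it through.** **1. The plan's own figures (Sample size section)**

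Inputs: 27 SMEs per arm, 65 per SME at baseline, 65% attrition, difference 0.25 SD, intra-cluster correlation 0.05, two-sided 0.05.

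- Retained per SME: 65 × 0.35 = 22.75, rounded to 23. Per arm: 27 × 23 = 621.
- Design effect: 1 + (23 − 1) × 0.05 = 2.10. Effective n per arm: 621 / 2.10 = 295.7.
- Power: 86.0% by the normal approximation, 84.7% by a t-test with 52 cluster degrees of freedom. The stated 85% reproduces.
- Overall, 54 × 23 = 1242 of 54 × 65 = 3510 participants would have follow-up data, so 65% would not.

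**2. What single imputation can do**

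The plan does not say which form is meant, so these are illustrations.

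- *No change from baseline:* 0.25 × 23/65 = 0.088 SD. The completers' effect is attenuated to about a third.
- *Imputed values counted as observed, with the SD and intra-cluster correlation taken as unchanged:* SE = √[2 × (1 + (m − 1) × 0.05) / (27 × m)]. For m = 23 this is 0.082 SD; for m = 65 it is 0.069 SD. Nominal power rises from 86% to 95% with no added information.

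**3. What complete case analysis can do**

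Assumptions not in the documents: retention differs between arms, and a normal latent tendency to stay has correlation ρ with the outcome. The mean shift among those retained is ρ × λ(p), where p is the retention proportion and λ(p) is the standard normal density at the cut-off divided by p. The bias is ρ × [λ(p₁) − λ(p₂)].

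| Retention by arm | λ(p₁) − λ(p₂) | Bias, ρ = 0.1 to 0.3 |
|---|---|---|
| 30% / 40% | 1.159 − 0.966 = 0.193 | 0.019 to 0.058 SD |
| 30% / 50% | 1.159 − 0.798 = 0.361 | 0.036 to 0.108 SD |
| 25% / 45% | 1.271 − 0.880 = 0.392 (before rounding) | 0.039 to 0.117 SD |

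The first two rows average 35% and 40% retention; the third averages the planned 35%. The range is about 0.02 to 0.12 SD against a target of 0.25 SD.

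**4. Does a MAR analysis remove that bias?**

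Not when retention depends on the unobserved outcome itself. Take 25% / 45% retention, ρ = 0.2 and an assumed baseline-outcome correlation of 0.5. Retention then correlates 0.2 × 0.5 = 0.1 with baseline.

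- Unadjusted bias: 0.2 × 0.392 = 0.078 SD.
- Bias after baseline adjustment: about (0.2 − 0.5 × 0.1) × 0.392 = 0.059 SD.

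A simulation on these inputs gave 0.078 and 0.058 SD. About three quarters of the bias remains. If retention depends on baseline only, even a baseline-adjusted complete-case analysis is unbiased.

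**The case against.** The strongest defence is that the rule is narrower than it looks. Inspection is limited to the amount of missingness and the assumptions; the treatment effect is not a criterion. Outcome analysts are blinded. The options are examples and include sound methods, and the analysis model is already named. All of this is true, and it lowers the risk of a result-driven choice. It does not supply a default, make MAR testable, or justify single imputation.

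Four stronger readings are tempting, and the documents do not support them.

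- *The method will be picked by its result.* A worst-case calculation, reporting the most favourable of four methods at nominal 0.05, gives a type I error of about 8% to 15% for correlations of 0.95 to 0.5 between test statistics. Given the stated criteria and the blinding, that is an upper bound, not an expectation.
- *Complete case flatly contradicts intention-to-treat.* The sentence mainly concerns allocation and adherence, and complete case is only one example. The sample size also already counts only participants with follow-up, so no planned power is lost. This is a tension, not a contradiction.
- *Single imputation gives 51% coverage.* Mean imputation at 65% missing, under MCAR and ignoring clustering, makes the SE 0.35 of its true size, and 2Φ(1.96 × 0.35) − 1 = 0.51. The plan does not specify that form. Imputing SME means and analysing at SME level keeps coverage at 95%.
- *The complete-case bias shows that the mixed model cures the problem.* Step 4 of the working shows that it does not under MNAR.

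**Conclusion.** The concern holds in limited form. The protocol forecasts 65% attrition, yet sets no default missing-data method for its primary analysis and defers the choice until the data have been inspected, on criteria that inspection cannot settle or that are already known. Single imputation should not be among the options, and complete case fits poorly with the stated analysis population.

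The sizes are illustrations. The attenuation to 0.088 SD applies to one form of single imputation. The bias of about 0.02 to 0.12 SD rests on assumed retention gaps and correlations, and because it arises from dropout related to the outcome, it argues for an MNAR sensitivity analysis rather than for the superiority of any MAR method. The power calculation is not in error. This should be fixed, but given the blinding and the restricted criteria it does not by itself undermine the trial.

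**What to change.** Amend the Missing data section, before unblinding, to say:

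- The linear or logistic mixed models of the Outcome evaluation section, fitted to all available baseline and follow-up observations with SME and participant random effects, are the primary approach to missing data, under MAR.
- Single imputation is removed.
- Complete case analysis is supportive only.
- A sensitivity analysis allows arm-specific departures from MAR, for example delta-adjusted multilevel multiple imputation, because the MAR model is itself biased if dropout depends on unobserved outcomes.

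Any bias figures quoted in support should be labelled as illustrations, with their assumptions. The cost is a change of wording and some extra analysis work; no new data are needed.

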### Ethical considerations

Ethics approval has been received from the institutional ethics committee from each of the local research officer’s institutions and the trial is registered with ISRCTN clinical trial registry (ISRCTN14104664).

### Duty of care

The duty of care protocol and standard operating procedures for local research officers established and used in the pilot study will be applied in the cRCT [53]. Contact information for international and local mental health services and supports and online links has been verified. Contact information for the local research officers has also been updated.

### Data protection

Data management and analysis will be controlled by MENTUPP consortium partners based at KU Leuven. The lead investigators of KU Leuven are responsible for developing and updating the data management plan, monitoring the implementation of the data management plan and managing the multi-country datasets. The Data Protection Officers of KU Leuven and UCC are responsible for the data security and privacy protection. KU Leuven is not involved in implementing interventions and collecting data and is only involved in accessing and analysing pseudonymised data. A Joint Data Controller Agreement was signed between members of the MENTUPP consortium to uphold their mutual roles and responsibilities. The use and transfer of participant data is covered by the EU GDPR, 2016 that ensures the protection of an individual’s privacy. Personal data will be collected as part of the informed consent process; however, the data will be stored separately from the evaluation data and will not be shared or reported outside the research team. A unique identification code will be generated for each participant [77] and will be used to link the log data from the MENTUPP Hub and the evaluation data across the time points and allow for participants to access, correct or withdraw any data at any time. The merged dataset will not include personal names, email addresses, mobile phone numbers or any identifiable information. Data will be transferred and stored following the principles of the EC Directive on personal data protection and confidentiality, GDPR (EC/2016/679).

